### 2.5. Sample Size and Power

Sample size is justified a priori following current recommendations [70], with all calculations derived analytically from noncentral *F*, t, and chi-square distributions at a two-tailed significance threshold of α = 0.05 and a target power of 1 − β = 0.80, reproducible in G*Power 3.1 (“ANOVA: Repeated measures, within factors”) and consistent with recent tutorials on power analysis for repeated-measures designs [63]. The primary test is a repeated-measures ANOVA (four within-subject levels) on each composite score. Assuming a correlation between repeated measurements of ρ = 0.50 (a typical value for repeated attitudinal ratings, to be verified in the pilot), the minimum sample is 24 participants for medium effects (*f* = 0.25) and 138 for small effects (*f* = 0.10); under the conservative assumption ρ = 0.30, these become 32 and 193, respectively. The minimum analyzable threshold is therefore set at *N* = 140 valid participants, sufficient to detect even small between-scenario effects under realistic conditions. Because these thresholds depend on ρ, an adaptive rule is pre-registered for the case in which the pilot estimate falls outside the assumed ρ = 0.30–0.50 range. The pilot returns $\hat{\rho }$ with a 95% confidence interval, and every threshold is recomputed at its lower bound, ρ_L_, which is the conservative choice. The number of valid participants required to detect *f* = 0.10 at power 0.80 is 274, 247, 220, 193, 165, and 138 for ρ_L_ = 0, 0.10, 0.20, 0.30, 0.40, and 0.50, respectively; an intermediate ρ_L_ is rounded down to the nearest tabulated value, so that the rule is fully determined in advance for any estimate the pilot can return. Two consequences follow. The recruitment target does not change because the requirement is a decreasing function of ρ and reaches only 274 in the theoretical worst case of ρ_L_ = 0; *N* = 300 preserves power ≥0.80 against small between-scenario effects for every value ρ can take, and the target is in any case set by the person-level analyses described below, which do not depend on ρ. The analytic floor does change: it is redefined as the value tabulated above for the observed ρ_L_, so that it remains at the pre-specified *N* = 140—rounded up from 138—only when ρ_L_ ≥ 0.50 and rises to 165, 193, 220, 247, or 274 as ρ_L_ falls to 0.40, 0.30, 0.20, 0.10, or 0. A ρ_L_ below 0.10 would in addition indicate that the composites are unstable across repetitions rather than that participants are inconsistent, and would therefore also trigger re-inspection of pilot reliability and of the measurement-invariance assumptions before the main study is launched. Any application of this rule, and the $\hat{\rho }$ that triggered it, will be recorded in the pre-registration and reported in the results article.

The recruitment target is *N* = 300 valid participants. This target is dictated not by the within-subjects effects (for which power at *N* = 300 is 0.99 for small effects at ρ = 0.50, with a minimum detectable effect of *f* = 0.07), but by the person-level analyses: the familiarity moderation (minimum detectable interaction *f*^2^ = 0.037 at *N* = 300), the global preference test (minimum detectable *w* = 0.21 on 5 degrees of freedom), and descriptive analyses of demographic subgroups. A small interaction effect (*f*^2^ = 0.02) would require *N* ≈ 550; H4 therefore remains partially exploratory, and a non-significant result will not be interpreted as evidence of absence. At *N* = 300, dependent pairwise comparisons detect differences from *dz* = 0.16 (uncorrected) and *dz* = 0.20 (at the Bonferroni bound for six pairwise comparisons), so all six scenario contrasts can be treated as confirmatory. Counterbalancing entails no loss of sensitivity for the primary comparisons: with sequence entered as a four-level between-subjects factor, the autonomy main effect retains 3 degrees of freedom and the same noncentrality, so the minimum detectable effect at *N* = 300 remains *f* = 0.07. The scenario × sequence interaction—the direct test of order dependence—carries 9 degrees of freedom and a minimum detectable effect of *f* = 0.08 at ρ = 0.50 (*f* = 0.10 at ρ = 0.30), giving power of 0.95 against a small order effect of *f* = 0.10; the serial-position main effect in the additive model carries 3 degrees of freedom and matches the sensitivity of the autonomy effect itself. Order artifacts large enough to masquerade as the hypothesized autonomy gradient are therefore detectable, rather than being assumed away. In the pilot, by contrast, the ascending and descending arms (*n* = 25 each) bound order effects only at *f* = 0.17, which excludes medium-to-large artifacts but not small ones; the definitive test is the main-study interaction. Table 2 summarizes the power analysis, and Figure 1 shows achieved power as a function of the number of valid responses.

After expected attrition is taken into account—approximately 85% of link visitors consenting, 96% of starters eligible after screening, 75% of eligible respondents completing (drop-out conservatively inflated to 25% given the 15–20 min repeated-block format), and 90% of submissions surviving quality-based exclusions [68]—approximately 545 link accesses (≈334 submitted questionnaires) are required to yield 300 valid responses (Table 3). The stopping rule is accrual-based: data collection continues until a minimum of 300 valid responses is reached; the absolute analytic floor is *N* = 140—or the higher value returned by the adaptive rule above, should the pilot estimate of ρ require it—below which the main study is not analyzed, and collection is extended. Drop-out between the first and last scenario blocks will be monitored by serial position across all four sequences as a fatigue indicator.

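### Section 2.5 claims power of at least 0.80 at N = 300 for every ρ and a floor rule complete for any pilot result; neither statement holds below zero

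*Protocol article*

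**What the plan says.** Section 2.5 plans the primary test as follows: "The primary test is a repeated-measures ANOVA (four within-subject levels) on each composite score". The design values are a "two-tailed significance threshold of α = 0.05 and a target power of 1 − β = 0.80". The pilot returns an estimate of ρ with a 95% confidence interval, and the thresholds are recomputed at the lower limit ρ_L. The table runs over ρ_L = 0, 0.10, 0.20, 0.30, 0.40 and 0.50: "The number of valid participants required to detect *f* = 0.10 at power 0.80 is 274, 247, 220, 193, 165, and 138".

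Three general statements are built on that table:

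- On the worst case, the section says that the requirement "reaches only 274 in the theoretical worst case of ρ_L_ = 0".
- On the recruitment target, it says that this sample size "preserves power ≥0.80 against small between-scenario effects for every value ρ can take".
- On the floor, a limit lying between two tabulated entries "is rounded down to the nearest tabulated value, so that the rule is fully determined in advance for any estimate the pilot can return".

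The section also says that a ρ_L under 0.10 leads to a second look at pilot reliability and measurement invariance before launch; it attaches no sample size to that step. Under the stopping rule in the same section, the main study is not analysed below the floor and collection goes on. Section 2.8 sets the pilot at 50 participants.

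**The concern.** The section itself notes that the required N falls as ρ rises. It follows that N keeps rising as ρ goes below zero, so zero is the worst case only if ρ cannot be negative. The text does not restrict ρ in that way, and a correlation among four repeated ratings is not bounded at zero.

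The floor rule has a separate gap. It acts on a lower confidence limit from 50 people, and that limit can be negative when ρ itself is clearly positive. The lowest tabulated value is 0, so a negative ρ_L has nothing below it to be rounded down to. Using the 0 row would mean rounding up, which reverses the rule's stated conservative direction.

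At stake are a power statement that is not true as worded and a rule presented as leaving no choice after the pilot. For some pilots it would leave one.

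**Working it through.** **Inputs.** All are from Sections 2.5 and 2.8 unless marked: m = 4 levels, α = 0.05, power 0.80, f = 0.10, target N = 300, pilot n = 50. Sphericity and a common correlation are assumed, as in the plan's own G*Power-type calculation. The interval method for ρ_L is not given in the article, so two methods are shown.

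**Formula.** Noncentral F with λ = m·N·f²/(1 − ρ), df1 = 3, df2 = 3(N − 1). Using 3(N − 4), to allow for the four sequences, leaves every required N unchanged and alters power at N = 300 by no more than about 0.0001.

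**Reproducing the plan.** At ρ = 0, 0.10, 0.20, 0.30, 0.40 and 0.50 the required N is 274, 247, 220, 193, 165 and 138. All six match. Power at N = 300 is 0.991 at ρ = 0.50, 0.949 at 0.30, 0.916 at 0.20 and 0.838 at 0.

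**Lower bound of ρ.** The sum of four ratings with equal variance σ² and common correlation ρ has variance 4σ²(1 + 3ρ). This cannot be negative, so ρ ≥ −1/3.

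**Extending the table below zero.** At N = 300 and f = 0.10, λ = 4 × 300 × 0.01/(1 − ρ) = 12/(1 − ρ). That is 12.00 at ρ = 0, 10.91 at −0.10 and 9.00 at −1/3.

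| True ρ | N needed | Power at N = 300 | Power at N = 274 |
|---|---|---|---|
| −0.05 | 288 | 0.818 | 0.779 |
| −0.09 | 299 | 0.802 | 0.761 |
| −0.10 | 302 | 0.798 | 0.757 |
| −0.20 | 329 | 0.759 | 0.716 |
| −1/3 | 365 | 0.709 | 0.665 |

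Power at N = 300 crosses 0.80 at ρ = −0.096.

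**How often is ρ_L negative with n = 50?**

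*Fisher interval for one pairwise correlation.* The half-width on the z scale is 1.96/√47 = 0.286, so ρ_L < 0 whenever the estimate is below tanh(0.286) = 0.278. At a true ρ of 0.30, arctanh(0.30) = 0.310 and the probability is Φ((0.286 − 0.310)·√47), about 0.44. A simulation of 20,000 pilots gave 0.42, hence about 43%. At a true ρ of 0.50 the same formula gives 0.0355.

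*F-based interval for an intraclass correlation over four ratings.* ρ_L < 0 when (1 + 3ρ̂)/(1 − ρ̂) is below the 97.5% point q of F(49, 147). The probability is P(F(49, 147) < q(1 − ρ)/(1 + 3ρ)).

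| True ρ | P(ρ_L < 0), single pair | P(ρ_L < 0), intraclass |
|---|---|---|
| 0.30 | about 43% | 1% |
| 0.50 | about 3.5% | 0% |

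In each of those pilots the rule as written returns no floor.

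**The case against.** The other side has good points, and several limit what can be concluded.

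- **A negative ρ_L does not make the power claim wrong.** A reader might infer that it does. Power at N = 300 depends on the true ρ, not on the pilot's lower limit. If the true ρ is 0.30 or 0.20, power at N = 300 is 0.949 or 0.916 whatever ρ_L turns out to be. This stands: the two faults are separate, and the power statement fails only for a true ρ below about −0.096.
- **The 300 target does not hang on these statements.** A reader might infer that it does. Section 2.5 says that the person-level analyses set the target and do not depend on ρ. This stands.
- **A floor above 300 is not implied.** The text ties the floor to the tabulated values, of which the highest is 274. Since accrual runs to at least 300, a floor of 274 would matter only if accrual fell short of it.
- **The low-ρ_L case is partly handled.** Every negative ρ_L triggers the reliability and invariance check. Section 2.12 locks pilot-based decisions before pre-registration and deposits the pilot data and code. Any choice would therefore be made before main-study data exist and would be auditable. This lowers the stakes, but the check supplies no N.
- **Zero is a natural bound in a random-intercept model.** Section 2.9.1 plans such a model for the position-adjusted estimate, and it implies a common correlation of at least 0. The power calculation and the floor, however, are for the repeated-measures ANOVA, which carries no such constraint, and Section 2.5 does not invoke one.
- **The interval method may be in the full analysis plan.** Its absence from the article is not held against the plan. It only explains why the probabilities above are a range.

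**Conclusion.** The point holds as a wording and completeness fault of minor weight.

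The claims about the worst case and about every value of ρ are false on the plan's own formula: 302 participants are needed at ρ = −0.10 and 365 at −1/3, the mathematical extreme. A negative average correlation between one person's attitude ratings is far from the planning range of 0.30 to 0.50, so this half has little practical effect.

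The claim that the floor rule is complete is also false, for any ρ_L below 0. How likely that is ranges from practically nil (intraclass interval, true ρ = 0.50) to about 43% (single-pair interval, true ρ = 0.30).

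These results assume sphericity, a common correlation and f = 0.10. They change no design feature, no enrolment figure and none of the tabulated values, all of which are correct.

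**What to change.** Make two changes in Section 2.5 and carry them into the pre-registration, before the pilot starts:

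1. Limit the power statement to ρ ≥ −0.09, or more simply to ρ ≥ 0, and delete the wording that calls 0 the worst case and the wording "preserves power ≥0.80 against small between-scenario effects for every value ρ can take".
2. Add one line to the rule: if ρ_L is negative, the floor is 274, and 0.80 power at that floor assumes a true ρ of at least 0.

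Optionally, name a pooled intraclass correlation over the four scenarios, with its own interval, as the pilot estimator. That makes a negative ρ_L rare within the planning range.

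The cost is a few sentences and a slightly less favourable stated property. No extra participants are needed. Settling the line before the pilot also avoids choosing it after ρ_L has been seen.

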### 2.6. Instrument and Measures

The instrument is a structured online questionnaire originally developed for this study, administered in Romanian in a single version distributed through a single link; the complete instrument (English translation) is reproduced in Appendix A. It comprises twelve sections: (1) informed consent and eligibility screening; (2) background and prior experience—AI familiarity (B1), experience with AI tools (B2), confidence in understanding medical information (B3), prior surgery and prior face/head/neck surgery (B4, B4a), healthcare contact frequency (B5), and trust in the national healthcare system (B6); (3) general attitudes toward AI in medicine (G1–G4, with G2 and G4 reverse-keyed for any composite); (4) the first attention check; (5–8) the four scenario blocks, administered in the sequence to which the participant was randomly allocated, each consisting of a vignette, a comprehension check, and an identical response block; (9) overall preferences and acceptability (P1–P4b); (10) the second attention check; (11) demographics (D1–D7: gender, age, education, occupational field, subjective financial situation, residence environment, development region); and (12) closing debriefing.

The per-scenario response block contains nine Likert items measuring the three primary dependent variables—acceptability (ACC1–ACC3), trust (TRU1–TRU3), and perceived risk (RSK1–RSK3)—followed by six responsibility items (RES1–RES4: surgeon, hospital, AI developer, unavoidable medical uncertainty; RES5: the surgeon’s moral duty to verify AI outputs; RES6: outcome-independent accountability), two manipulation-check items (MAN1: perceived AI control over the final surgical decision; MAN2: perceived technical sophistication of the system), and a perceived difficulty item (DIF1). All scaled items use 7-point end-anchored Likert response formats. Composite scores are computed as the arithmetic mean of their items after reverse-scoring RSK1 (8 − score), which is the only reverse-keyed item in the response block; higher risk scores indicate higher perceived risk. Treating item means on end-anchored 7-point scales as quasi-continuous interval variables is standard practice in experimental vignette research; ordinal-model sensitivity analyses are nevertheless planned in line with current guidance on Likert-based outcomes [62,71]. Table 4 summarizes the measurement structure; per-scenario variables carry the scenario suffix (e.g., ACC1_A, ACC1_B, ACC1_C, ACC1_D).

Because everyday usage collapses several distinct notions into one, the instrument separates them explicitly, and the header shown to participants states the intended sense. RES1–RES3 measure agent-directed responsibility—how much of the responsibility for an error each party should bear—and appear, together with RES4, under a common header that states that responsibility may be shared and that each party is to be rated separately rather than as a share of a fixed total, so that both diffusion and concentration are expressible; the header also glosses responsibility as answering for the error and putting it right, expressly distinguishing it from being found at fault in court. RES4 is not an agent and captures the alternative attribution that an error reflects irreducible clinical uncertainty; it is analyzed separately and is excluded from the concentration index. RES5 isolates moral responsibility from legal fault by construction (“even if the surgeon were not legally at fault…”), and RES6 isolates accountability in its outcome-independent sense—whether answerability depends on how the operation turned out—which is precisely what separates accountability from outcome-based blame. Legal liability proper is not measured per scenario. It is asked once, globally, and separately from the ethical claim, as two items presented on the same page and scale: P4a, that the surgeon should always remain legally responsible for any surgical outcome, and P4b, that the surgeon should always remain ethically responsible for it. Keeping them apart matters because a single double-barreled item would force the two notions to move together and would conceal exactly the pattern the responsibility literature predicts—a surgeon held morally answerable for an outcome to which no legal fault attaches. Both are analyzed descriptively and against RES5 and RES6, and their difference within participants—the extent to which a respondent holds the surgeon morally but not legally answerable—is itself reported. They are not treated as within-scenario outcomes, because lay judgments of legal liability depend on doctrinal assumptions that a short vignette cannot supply and that vary with the respondent’s exposure to the legal system; treating such judgments as a repeated-measures outcome would attribute a precision to them that they do not have. The Romanian wording of these items avoids the terms “culpă” and “răspundere juridică” except where legal fault is explicitly intended, and the pilot cognitive interviews (Section 2.8) probe specifically whether participants read RES1–RES3 as moral answerability, as causal contribution, or as legal liability. If the interviews reveal systematic conflation, the header wording will be revised, and the items retested before pre-registration, and the change documented.

### 2.7. Data Quality Procedures

Four mechanisms protect data quality, consistent with current best-practice recommendations for careless-responding prevention and detection [68,69] and with multi-layered approaches to online-survey integrity [72]. First, two attention checks are embedded in the questionnaire: ATT1, an instructed-response item placed after the general attitudes section (participants are asked to select a specific scale point regardless of their opinion), and ATT2, a content check after the scenario blocks asking which type of surgery the scenarios described. Exclusion applies only when both checks are failed. Second, each vignette is followed by a single multiple-choice comprehension check targeting the scenario’s defining feature (who made the final decision, or what the AI’s role was). A first incorrect response triggers branching that re-presents the full scenario, after which the check is repeated; a second incorrect response flags that scenario as failed (CC_*x*_FAIL = 1), and participants failing at least two of the four scenarios are excluded. Third, invariant response patterns (identical responses to all Likert items, including across scenarios) and duplicate records are screened during data cleaning. Fourth, all closed questions are mandatory on the survey platform, structurally preventing item-level missingness in the dependent variables; “prefer not to answer” options exist only for selected background and demographic items (B4, B4a, B5, B6, D1, D6, D7) and are coded as a distinct category descriptively and as missing in inferential models; participants who decline the separate explicit consent for the two health-related items (Section 2.10) are not presented with items B4 and B4a, and those records are coded in the same way. The platform does not record completion time, so data quality relies on the checks above rather than on a temporal filter; this is declared as a limitation. Finally, each participant’s sequence allocation (SEQ) is made at the point of entry to the scenario blocks and written to the submitted record, and the platform maintains its page counters separately for each sequence. Drop-out can therefore be attributed to a sequence and a serial position even where no submission is stored. Balance across the four sequences is monitored during accrual and reported in the participant-flow diagram, and section-wise drop-out is tabulated by serial position as well as by scenario, so that fatigue can be distinguished from a reaction to a particular scenario. The comprehension checks remain valid under counterbalancing because each is bound to the scenario it immediately follows, and ATT2 concerns content common to all four scenarios.

### 2.8. Pilot Study and Instrument Validation

The instrument will be validated in a pilot study (*N* = 50, not included in the main sample, allocated 1:1 to the ascending sequence A → B → C → D and to its exact reverse D → C → B → A) before the main study is launched. The pilot will estimate (i) internal consistency—Cronbach’s α and McDonald’s ω with 95% confidence intervals for each three-item composite, computed separately per scenario, against a threshold of ≥0.70, with ω reported alongside α in line with current psychometric guidance [73]; with three items per construct, α ≥ 0.70 requires a mean inter-item correlation of only $\bar{r}$ ≥ 0.44 under the generalized Spearman–Brown relation (Figure 2), a realistic requirement for parallel items; (ii) inter-item correlations (flagged at r > 0.90 for redundancy or r < 0.20 for heterogeneity) and corrected item-total correlations (threshold ≥ 0.40), plus the correlation between repeated measurements, reported with a 95% confidence interval, to verify the ρ ≈ 0.50 planning assumption and, where it is not met, to trigger the adaptive sample-size rule of Section 2.5; (iii) the factor structure of the nine response items, via exploratory factor analysis (principal-axis extraction, oblique rotation, sampling adequacy KMO ≥ 0.70, Bartlett’s test of sphericity, parallel analysis as the retention criterion)—an anticipated risk is that acceptability and trust items form a single factor, in which case the two constructs will be merged into a single “trust–acceptance” score and the analysis plan adjusted transparently before pre-registration, with this decision taken exclusively on pilot data; (iv) first-attempt comprehension-check pass rates per scenario (threshold ≥ 70%); (v) manipulation validity—MAN1 scores must order the scenarios from A to D in both pilot arms, while MAN2 (perceived technical sophistication) must not increase monotonically with autonomy; if it does, the vignettes will be reworded to equalize the described sophistication of the systems and the check repeated before pre-registration; (vi) fatigue—perceived difficulty (DIF1) and section-wise drop-out across serial positions in both arms; (vii) cognitive interviews with 5–8 participants to identify confusing wording, probing in particular whether RES1–RES6 are read in the intended senses of moral answerability, outcome-independent accountability, and legal fault (Section 2.6); and (viii) a first bound on order effects—the two pilot arms are compared on the three composites and on MAN1 by a scenario × order mixed ANOVA (*n* = 25 per arm; minimum detectable interaction *f* = 0.17 at ρ = 0.50), which can exclude medium-to-large order artifacts but not small ones, the definitive test being the main-study interaction. The four-sequence randomizer used in the main study is implemented in the same pilot build. Because the pilot itself exercises only two of the four arms, the randomizer is verified there by simulated allocation, which also confirms that the allocated sequence and the serial position of each scenario are stored correctly. A ninth objective is included: (ix) the keying and dimensionality of the four general-attitude items (G1–G4), since G3 is a caution item that the present scoring treats as positively keyed while G2 and G4 are reversed; the scoring rule for that block is fixed on pilot data before pre-registration, and if the four items do not form a single interpretable dimension they will enter the person-level analyses individually rather than as a composite. Because a sample of 50 is at the lower limit for stable factor solutions, the pilot EFA is treated as provisional: the factor structure will be re-examined by confirmatory factor analysis on the main sample (*N* = 300), with acceptable fit defined a priori as CFI/TLI ≥ 0.95, RMSEA ≤ 0.06, and SRMR ≤ 0.08. Because the same nine items are answered four times, longitudinal measurement invariance across the four scenario repetitions (configural, metric, and scalar) will also be tested on the main sample; at least partial scalar invariance is required for the between-scenario comparison of composite means, and any non-invariant item will be reported and handled by partial-invariance modeling. Pilot results will be reported in the methods section of the results article.
